### Aims

The main aims of this study are to:

1. Describe the evolution of early neurobehavioural development in infants <30 weeks from birth to two years’ CA compared with children born at term, and to explore how neurobehaviour is influenced by perinatal variables.

2. Explore the relationship between early neurobehavioural development and neonatal brain abnormalities (development and injury) at term using multi-modal MRI in infants <30 weeks at birth.

3. Investigate the predictive validity of neurobehavioural assessments during the early neonatal period for developmental outcomes at one and two years’ CA in infants <30 weeks at birth.

4. Examine symptoms of depression, anxiety, and post-traumatic stress in mothers and fathers of infants <30 weeks at birth and to describe changes in parental psychological wellbeing over the first two years of the child’s life compared with children born at term.

5. Examine parental psychological wellbeing, and parent and family factors during the neonatal period as predictors of development at one and two years’ CA in children born <30 weeks, and whether these relationships are similar in children born at term.

In addition, secondary aims of this study are to:

1. Explore whether neurobehavioural examinations in the preterm period relate to concurrent physiological status (i.e. heart rate and oxygen saturations) in infants <30 weeks at birth.

2. Describe the parenting beliefs and practices of parents of infants <30 weeks at birth across the first two years of the child’s life.

3. Examine whether parental psychological wellbeing from birth to one year CA is associated with the parent–child relationship and child development when the child is one and two years’ CA in infants <30 weeks at birth.

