### Outcomes at one and two years’ corrected age (both preterm and term infants)

At one and two years’ CA families will be contacted to participate in follow-up. The child will have a developmental assessment, both parents will be asked to participate (separately) in a parent–child interaction task, and both parents will be asked to complete a set of questionnaires.

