#### Parental assessment

Parent questionnaires will be collected at multiple time points. The first will be when their infant has their first neurobehavioural assessment. Both parents will then be asked to complete questionnaires fortnightly until term equivalent age, at term equivalent age, at three and six months, and at six-monthly intervals until the child’s second birthday (CA). The questionnaires at 3, 6 and 18 months will be posted to families, and asked to be returned to the investigators in a prepaid envelope. Parents will be sent text messages as a reminder to complete questionnaires. The term, one and two year questionnaires will be completed at the time of the infant’s follow-up assessments. Not all measures will be collected at all time points. Each questionnaire to be used in the study is described in Table 4. The time taken to complete these questionnaires will vary from 5 minutes at earlier ages to approximately 2 hours (total) at 24 months’ CA.

**Table 4 T4:** Description and purpose of parental questionnaires

**Assessment**	**Purpose**
CES-D	The *Centre for Epidemiological Studies Depression Scale (CES-D)*[62] will be used to measure depressive symptoms. The questionnaire consists of 20 questions (total score range 0 to 60) with higher scores representing greater depressive symptoms. A score ≥16 on the CES-D represents significant depressive symptoms. This threshold has been shown to correlate well with clinician ratings of depression [63]. The CES-D has been used extensively in general populations and has been used with parents of preterm infants [64,65].
HADS	The *Hospital Anxiety and Depression Scale (HADS)*[66] will be used to assess anxiety. The HADS assesses symptoms of anxiety and depression using 7 items for each scale that are scored with a 4-point rating scale (total score range 0 to 21). Scores above 11 are considered to indicate significant symptoms of depression or anxiety. The HADS has been validated in a variety of settings and has been found to perform well in assessing the severity of anxiety disorders and depression, not only in primary care patients and the general population [67] but also in parents of preterm infants [68].

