Parenting practices questionnaire	The *Parenting Practices Questionnaire* is a 16-item measure that assesses parental warmth, hostility and involvement with their child (Longitudinal Study of Australian Children, LSAC).
ITSEA	The *Infant Toddler Social and Emotional Assessment*[76] (ITSEA) is a 135 item parental report measure of social–emotional problems and competencies in 1 to 3 year olds. It assesses 4 broad domains of behaviour: dysregulation, externalizing, internalizing and competencies. Mean scores below the 10^th^ percentile for competence, or above the 90^th^ percentile for externalising, internalising and dysregulation suggest the infant may be at risk for psychopathology. The ITSEA has good internal consistency, validity, and test-retest reliability, and has been used extensively, including with very preterm populations.
MacArthur CDI	The *MacArthur-Bates Communicative Development Inventories (CDI)*[77] are standardised parent report forms for assessing early language (semantic and grammatical) development in 16 to 30 month old children. The CDI: Words and Sentences (Toddler form) will be completed by the primary care-giver.
FAD	The *Family Assessment Device (FAD)*[78] requires the primary caregiver to indicate whether they “strongly agree”, “agree”, “disagree”, or “strongly disagree” with 60 statements about family functioning. The inventory yields 7 scales: problem solving, communication, roles, affective responsiveness, affective involvement, behaviour control and general functioning. Higher scores indicate poorer family functioning.
ITSP	The *Infant/Toddler Sensory Profile Questionnaire* (ITSP) [79] consists of 48 questions, addressing 6 sensory processing sections, including: Auditory, Visual, Tactile, Vestibular, and Oral Sensory Processing, as well as a General measure. Questions within each sensory processing section yield information about how the child responds to stimuli in each sensory system. Its purpose is to evaluate the possible contributions of sensory processing to the child’s daily performance patterns, to provide information about his or her tendencies to respond to stimuli and to identify which sensory systems are likely to be contributing to or creating barriers to functional performance. The ITSP has excellent content validity and adequate to excellent reliability [80].

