CSBS-DP	The *Infant-Toddler checklist* from the *Communication and Symbolic Behavior Scales Developmental Profile* (CSBS-DP) [81] is a 24 item screening tool designed to measure 7 predictors of language including emotion and eye gaze, communication, gestures, sounds, words, understanding and object use in children aged between 6 and 24 months of age.
Social Risk Index	A *Social Risk Index* (family demographic questionnaire) [37] score will be calculated based on a combination of family structure, education of primary caregiver, employment of primary income earner, language spoken at home and maternal age at the birth of the child. Higher scores indicate higher social risk.

Table 5 provides an overview of the questionnaire measures to be collected at each time point. For term-born infants, birth and term are the same time point in Table 5.

**Table 5 T5:** Administration timetable for parent completed questionnaires

	**Birth**	**F/night***	**Term**	**3mth (CA)**	**6mth (CA)**	**12mth (CA)**	**18mth (CA)**	**24mth (CA)**
CES-D	√	√	√√	√√	√√	√√	√√	√√
HADS	√	√	√√	√√	√√	√√	√√	√√
PCL-S			√			√		√
IPIP-NEO	√							
PSOC					√√	√√		√√
PSI-LSS	√√					√√		√√
CISS	√√				√√			
Demographic & family questionnaire	√√							
Parent mental health history questionnaire			√√			√√		√√
Parenting practices					√√	√√		√√
ITSEA						√√		√√
MacArthur CDI								√√
FAD								√√
ITSP								√√
CSBS-DP								√√
Social Risk Index	√√					√√		√√

Note. *F/night = administered fortnightly from first neurobehavioural assessment until term equivalent age; √√ = both preterm and term-controls; √ = preterm only; CES-D = Centre for Epidemiological Studies Depression Scale; HADS = Hospital Anxiety and Depression Scale; IPIP-NEO = International Personality Item Pool Five Factor Personality Inventory-NEO, PCL-S = Posttraumatic Stress Disorder Checklist Specific Version; CISS = Coping Inventory for Stressful Situations; PSOC = Parenting Sense of Competence Scale; PSI-LSS = Parenting Stress Index – Life Stress Scale; ITSEA = Infant-Toddler Social and Emotional Assessment, MacArthur CDI = MacArthur Communicative Development Inventories, FAD = Family Assessment Device, ITSP = Infant Toddler Sensory Profile, CSBS – DP = Communication and Symbolic Behavior Scales Developmental Profiles.

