3. The validity of early neurobehavioural assessments from birth to term-equivalent age for predicting development at one and two years’ CA in very preterm children will be investigated using separate linear (continuous outcomes) and logistic (binary impairment outcomes) regression models for each neurobehavioural assessment time point according to chronological and gestational age and each outcome. Estimates of the regression coefficients and the R^2^ values (representing the proportion of variability in the outcome explained by the model) from these models will be compared with estimates from the same models using neurobehaviour at term equivalent age as the predictor to obtain an idea of the predictive ability of these early measurements compared with the measurements at term as used currently. Data from term-born controls will be used to provide a local-reference population for calculation of mild, moderate and severe developmental impairment (mild = more than 1 SD below the mean, moderate = more than 2 SD below the mean, severe = more than 3 SD below the mean on the Cognitive Composite Scale on the Bayley-III).

4. To examine symptoms of depression, anxiety, and post-traumatic stress in mothers and fathers of very preterm children at birth during the first two years of the child’s life compared with term-born controls, we will present means and 95% CI for each parental assessment at each time point. For each time point, the observation closest to the specified time for the completed week within +/− 3.5 days for weekly assessment and +/− 7 days for fortnightly assessments will be selected for each individual.

5. To examine the relationships between parental psychological wellbeing, parent and family factors, and very preterm children’s neurobehavioural development at birth, and later two year-old cognitive, motor and social-emotional developmental outcomes, we will fit separate linear regression models for each of the two year outcomes. Initially each parent and child factor will be explored using separate univariable models for each outcome before combining important factors into a single model for each outcome to assess independent predictors.

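### For the two-year social-emotional outcome, Aim 5 takes no step to separate the parent who rates the child from the parent whose distress is the predictor, so part of any association may be reporting bias

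*Protocol article*

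**What the plan says.** All references are to the protocol article.

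- **Aim.** Main aim 5 (Aims) is to "Examine parental psychological wellbeing, and parent and family factors during the neonatal period as predictors of development at one and two years" corrected age in the preterm children.
- **Analysis.** Data collection & analysis, item 5, takes the child's "later two year-old cognitive, motor and social-emotional developmental outcomes, we will fit separate linear regression models for each of the two year outcomes". Each factor is first examined univariably, and the important ones are then combined in one model per outcome to find independent predictors.
- **Predictors.** Table 4 (Parental assessment) says that the CES-D "will be used to measure depressive symptoms" and the HADS "will be used to assess anxiety". Parents of preterm infants also complete the PCL-S. All three are parent-completed questionnaires.
- **Social-emotional outcome.** In Table 4 the ITSEA "is a 135 item parental report measure of social–emotional problems and competencies in 1 to 3 year olds". Table 5 lists it with the parent-completed questionnaires at 12 and 24 months. Item 5 does not name it.
- **Who rates.** At follow-up "both parents will be asked to complete a set of questionnaires". The ITSEA entry names no rater, whereas the CDI and FAD entries assign those forms to the primary caregiver.
- **Other two-year outcomes.** Developmental assessment says that developmental outcomes are assessed blind. Table 2 describes the Bayley-III as covering cognition, language and motor skills.

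**The concern.** If the mother's neonatal distress predicts the mother's own ITSEA ratings, predictor and outcome come from one reporter. Distress can persist, and a parent who is distressed when completing the form may describe the same child as more difficult. An association can then arise without any difference in the child.

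The bias would run towards the expected result, that parental distress goes with child social-emotional problems. The Background section motivates the parental part of the study with this link, and the Discussion promises to examine what parental distress implies for child development. The univariable screen adds to the problem, because a reporter-driven association helps a distress score enter the combined model.

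**Working it through.** The plan gives no figure to reproduce, so the check traces the raters and then illustrates the size.

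**1. Raters set side by side.**

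| Element of Aim 5 | Instrument | Source of the rating |
|---|---|---|
| Parental distress | CES-D, HADS, PCL-S | the parent |
| Cognitive, motor outcome | Bayley-III | blinded assessor |
| Social-emotional outcome | apparently ITSEA | a parent, not specified which |

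The ITSEA is inferred, because no other broad social-emotional measure at two years is described. The Emotional Availability Scales are coded from video, but they measure the parent–child relationship and belong to secondary aim 3. Separate models by parent are stated for secondary aims 2 and 3. For Aim 5, where a parent appears to rate one of the outcomes, they are not.

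**2. Mechanism under no true effect.** Let ρ be the correlation between the rating parent's neonatal and 24-month distress. Let b be the standardised effect of current distress on that parent's rating. If neonatal distress has no other path to the rating, the spurious correlation is r = ρ × b.

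**3. Chance of a significant result.** By Fisher's z, for a two-sided 5% test:

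P = Φ(atanh(r)·√(n−3) − 1.96) + Φ(−atanh(r)·√(n−3) − 1.96)

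Inputs: n = 150 preterm infants (Sample size section). ρ and b are assumptions; the document gives neither.

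Worked case, ρ = 0.5 and b = 0.3: r = 0.15, atanh(r) = 0.151, √147 = 12.12, product 1.83. Φ(1.83 − 1.96) is about 0.45 and the second term is negligible, so P = 45%. With n = 120 the same r gives 37%.

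**4. Range at n = 150** (spurious r, then P):

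| ρ | b = 0.1 | b = 0.2 | b = 0.3 | b = 0.4 |
|---|---|---|---|---|
| 0.3 | 0.03, 6.5% | 0.06, 11% | 0.09, 19% | 0.12, 31% |
| 0.5 | 0.05, 9% | 0.10, 23% | 0.15, 45% | 0.20, 69% |
| 0.7 | 0.07, 14% | 0.14, 40% | 0.21, 73% | 0.28, 94% |

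The Sample size section sets 0.2 as the smallest correlation to be identified, for Aims 2 and 3. The upper end of this grid reaches that size. The calculation covers one univariable test in which every rating comes from the exposed parent. It does not model the combined regression.

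**5. What each sensitivity analysis can do.**
- *Adjusting for the rater's 24-month distress.* Under the mechanism in step 2, the coefficient of neonatal distress falls to zero once current distress is in the model. If a real effect on the child runs through continuing distress, that part is removed too.
- *Pairing one parent's distress with the other's rating.* ρ is replaced by the correlation between one parent's neonatal distress and the partner's 24-month distress. If that were 0.3 with b = 0.3, r would still be 0.09 and P 19%, even with all 150 families. The bias shrinks but does not vanish.

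**The case against.** The strongest reply is that the document does not say that the exposed parent rates the child. Item 5 names neither the instrument nor the rater, and pairing across parents is compatible with the text. A condensed article may leave such pairing to the full protocol. This stands as far as it goes: a reader might infer that predictor and outcome always share a reporter, and the document does not establish that. The point therefore applies where the same parent supplies both, which the stated model permits and does not examine.

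Other parts of the reply also stand:

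- The predictor is neonatal, about two years before the rating. This weakens the bias but does not remove it, since the Background itself expects some parents to remain distressed at one and two years.
- Useful data are already scheduled: CES-D and HADS at 24 months, and neuroticism in preterm parents, which could partly stand in for a lasting negative reporting style. It would therefore be too strong to say that reporting bias could never be told apart from a real association. The gap is that Aim 5 plans no use of these data for that purpose.
- A reader might infer that the plan will wrongly rank social-emotional above cognitive and motor outcomes. The models are separate and no such contrast is planned.
- Social-emotional development is one of three outcomes in the fifth main aim, and the wording is of relationships and predictors. The point does not reach the study as a whole.

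**Conclusion.** The point holds in a limited form. Aim 5 models what appears to be a parent-reported outcome on parents' self-reported distress, with no informant step. Where one parent supplies both, an association may be partly reporting bias, in the direction of the expected finding. The cognitive and motor outcomes are untouched.

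The size is unknown. The span from 6.5% to 94% follows wholly from assumed values of ρ and b. It shows that the bias could be trivial or serious, and no single figure in it, including 45%, should be read as this study's error rate.

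A reader might also conclude that the cross-informant model ought to replace the planned one. The document does not support that. It does not guarantee two ITSEAs per family, and restricting to two-rater families could select on family structure, which is itself a component of the Social Risk Index. Sensitivity analyses and a limit on the conclusion are the proportionate request.

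**What to change.** Keep the planned Aim 5 model. For the social-emotional outcome only:

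1. State that the outcome is the ITSEA, if that is so, and record which parent completed each form.
2. Fit mothers and fathers separately, as secondary aim 3 already does.
3. Pre-specify two sensitivity analyses: (a) one parent's neonatal distress against the other parent's ITSEA, in families where both rated; (b) the same-informant model adjusted for the rater's 24-month CES-D and HADS.
4. State that the same-informant association alone will not be taken to show that parental distress affects the child's social-emotional development.

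Cost: mainly analysis wording and one recorded item. Table 5 already schedules the 24-month CES-D and HADS for both groups, so (b) needs no new instrument. Analysis (a) will have fewer families and less precision, may be selective on family structure, and leaves some bias if partners' distress is correlated. Analysis (b) may remove some real effect. The two are best read together, with neither replacing the planned model.

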### Secondary aims

1. To explore whether the neurobehavioural trajectory varies according to concurrent physiological status, physiological status variables of interest will be dichotomised or separated into distinct categories (e.g. stable versus unstable). The mean (and 95% CI) scores at each time point (as described above) will be plotted separately for children within each category. Trends over time will be modelled using separate mixed effects regression models for each of the neurobehavioural scores including a fixed effect for time (gestational and chronological age) and physiological status and an interaction between time and physiological status to assess whether the effect of time is different in the different categories of this variable.

2. To describe the parenting beliefs and behaviour of parents of very preterm children across the first two years of the child’s life compared with term-born controls, we will present means and 95% CI for each parental assessment at each time point from term equivalent age to two years. Trends over time will be compared between the two groups using separate mixed effects regression models for each parent, with a fixed effect of time (gestational and chronological age) and group as well as an interaction between time and group. Models will also include a random effect to allow for repeated measures within a parent.

3. To examine whether parental psychological wellbeing is associated with the parent–child relationship when the child is one and two years’ CA, average scores for parental mental health from birth to 6 months, and from one to two years will be used as predictors of the 6 outcomes scales of the parent–child relationship measure at one and two years CA respectively. Separate linear regression models will be used for mothers and fathers to examine these relationships.

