Each examination will be video-recorded so that assessments can be scored later as appropriate. As infants prior to term age in the NICU can be sensitive to handling we will not administer any item considered to cause the infant unnecessary stress. During the assessment, we will simultaneously observe pulse oximetry data, which will give information on oxygen saturations and heart rate. If these data and other behaviour, such as apnoea, suggest increased stress levels in the infant as a result of the neurobehavioural assessment, administration of that item will cease. The assessment will be continued where possible. Due to the poor self-regulation abilities and sensitivity to handling of infants younger than 30 weeks’ GA, it will be necessary for early evaluations (<30 weeks’ GA) to principally involve observation, focusing on: GMs [40], state, motor and autonomic regulation and the infant’s response to external stimuli. Behavioural (e.g. colour changes, facial expressions) and motor observations (e.g. postural tone and quality of spontaneous movements) will be video-recorded during a standard care procedure (e.g. a nappy change) to evaluate the infant’s response to handling during an everyday activity. The video recordings will allow the assessor to make more detailed assessments than they are able to do in real-time and allow for inter-observer reliability of scoring (two scorers will be used to assess reliability). Evaluations will be completed weekly from enrolment up to 32 weeks’ GA, then fortnightly until term, or discharge from the Royal Women’s Hospital. Assessments will be timed to coincide with care procedures to ensure the infants’ sleeping patterns are not disrupted. Initially assessments will take approximately 15 minutes and increase to 30 minutes as the infants become older and more stable, enabling us to elicit more specific responses.

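### Secondary aim 1 categorises continuous heart rate and oxygen saturation, leaves unclear whether status can change between examinations, and directs its stated test at the time interaction rather than at the concurrent relation

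*Protocol article*

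**What the plan says.** All references are to the protocol article.

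- **Aims, secondary aim 1.** The question is to "Explore whether neurobehavioural examinations in the preterm period relate to concurrent physiological status (i.e. heart rate and oxygen saturations"), in the preterm group.
- **Serial neurobehavioural assessments up to term.** On measurement: "During the assessment, we will simultaneously observe pulse oximetry data, which will give information on oxygen saturations and heart rate". On frequency: "Evaluations will be completed weekly from enrolment up to 32 weeks’ GA, then fortnightly until term, or discharge from the Royal Women’s Hospital".
- **Secondary aims, item 1 (analysis).** The physiological variables "will be dichotomised or separated into distinct categories (e.g. stable versus unstable"). Mean scores at each time point "will be plotted separately for children within each category". The mixed model has a fixed effect for time and also includes "physiological status and an interaction between time and physiological status". The given reason for the interaction is to see whether the time effect differs between categories.

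The only example in the categorising sentence is the choice of labels. Categorising itself is a firm commitment, and no continuous analysis is offered for this aim.

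**The concern.** There are three linked problems.

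1. **Information.** Heart rate and oxygen saturation are continuous. Grouping them discards the differences within each group and makes a real association harder to find.
2. **Unit of the category.** An infant may be examined many times between enrolment and term, and physiology can change over that period. The plan follows the layout used for MRI injury under main Aim 2, where each child has one finding at term. That layout suits a fixed characteristic. Here the plan does not say whether status is reassigned at each examination.
3. **Target of the test.** The aim asks whether the score and physiology go together at the same examination. The analysis asks whether trajectories differ between categories.

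At stake is interpretation. A null interaction would not mean that score and physiology are unrelated. A difference between categories could reflect sicker versus healthier infants, moment-to-moment fluctuation, or both.

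**Working it through.** **Plan's own figure.** The protocol gives no power or precision figure for secondary aim 1. The Sample size section covers main Aims 1 to 3 only. Its precision figure for a mean reproduces: 1.96/√150 = 0.160 SD. It says nothing about this analysis.

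**Step 1: information kept after categorising.**

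Assumptions, not in the protocol: a normal covariate and a linear relation. For two groups with share p in one of them, the fraction kept is φ(z_p)²/[p(1−p)].

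| Split | φ(z_p) | Calculation | Kept |
|---|---|---|---|
| 50/50 | 0.3989 | 0.3989²/0.25 | 64% |
| 80/20 | 0.2800 | 0.2800²/0.16 | 49% |
| 90/10 | 0.1755 | 0.1755²/0.09 | 34% |

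The protocol also allows more than two groups. For k equal groups, the fraction kept is the average of the squared group means of a standard normal variable.

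- Three groups: means −1.091, 0 and 1.091, so (2 × 1.091²)/3 = 0.79.
- Four groups: means ±1.271 and ±0.325, so (2 × 1.271² + 2 × 0.325²)/4 = 0.86.

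The protocol gives no cut-points or group sizes, so the range is the result and no single row can be picked out.

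**Step 2: does it matter whether the label belongs to the child or to the examination?**

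This was checked with an illustrative simulation in which every effect size is assumed. It used 150 infants with six examinations each, a covariate of total variance 1, a within-infant effect of 0.1, random-intercept and residual SDs of 0.7, and 100 runs per setting. The mixed model had time, status and their interaction, and the test was on the status term. Categories were split at zero, either at each examination or on the infant's mean. ICC is the share of covariate variance that lies between infants.

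| ICC | Between-infant effect | Continuous | Category per examination | Category per child |
|---|---|---|---|---|
| 0.3 | 0 | 91% | 69% | 3% |
| 0.3 | 0.1 | 93% | 76% | 16% |
| 0.6 | 0 | 58% | 37% | 7% |
| 0.6 | 0.1 | 80% | 48% | 19% |

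With 100 runs the Monte Carlo standard error is at most √(0.5 × 0.5/100) = 5 percentage points. A category per examination still detects the relation, with less power. A category per child largely misses it. When the relation is purely within-infant, its power is close to the 5% error rate.

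**Step 3: what the interaction tests.**

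Write the score as a + b·time + c·status + d·time·status + error. A concurrent relation that is the same at every age has c ≠ 0 and d = 0. A test of d then has no power beyond its error rate, however large c is. The stated test would therefore not detect a constant concurrent relation. The status term c is in the model, but the plan does not name it as the quantity to report.

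**The case against.** **A reader might infer that the category is attached to the child and that the concurrent relation is not tested at all.** The protocol does not establish this. The phrase about plotting children within categories matches the Aim 2 MRI wording, but it follows a reference to each time point, so it can equally mean the children who fall in each category at that time. The analysis text itself calls the status concurrent. The model includes status as its own fixed effect, and a mixed model accepts a covariate that changes by examination. On that reading the status term does address the concurrent relation, with less power and with between-infant and within-infant differences mixed. This objection stands. The unit is ambiguous, and the per-child results in Step 2 are conditional.

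**A reader might turn the retained fractions into an effective sample size**, for example 0.64 × 150 ≈ 95 infants. That does not carry over. It presumes one observation per infant and a two-group split, while the plan has repeated examinations and allows more groups. Oxygen saturation is capped at 100%, so normality is also doubtful. The fractions show direction and rough size only.

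**Storage of the data.** The protocol says pulse oximetry is observed during the assessment. It does not say that values are stored for each examination. Storage is implied by the aim but needs confirming.

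**Level of detail.** Cut-points and coding rules are commonly left to an analysis plan, and their absence from a condensed article is no fault. Categorising is different, because the article commits to it.

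**Choice of question.** The analysis text openly states a trajectory question, and the interaction fits that question. The mismatch is with the wording under Aims. It is one of emphasis, since the status term is also in the model.

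**Conclusion.** The point holds in a limited form. The protocol commits to categorising measures that it defines as heart rate and oxygen saturation. It does not make clear that status can change between examinations, and it directs the stated test at the interaction although the aim concerns the concurrent relation.

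Under assumed normality and linearity, the loss is at least about 36% of the information with two groups, and about 14% to 21% with four or three equal groups. An unequal two-group split loses more. If the label were fixed per child, a within-infant relation would be largely missed; that size rests on the assumed simulation settings and on a reading that the text permits but does not state.

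This is an exploratory secondary aim with no power claim attached, so the consequence for the study as a whole is small.

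**What to change.** Keep the planned mixed model for secondary aim 1 and change the exposure and the reporting:

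1. Enter the heart rate and oxygen saturation values from each examination as continuous, time-varying covariates, with a flexible term such as a spline if the relation is not linear.
2. Separate each covariate into the infant's own mean and the deviation from it at that examination, so that differences between infants and fluctuation within an infant are estimated apart.
3. Report the concurrent association as the answer to the aim, and the time interaction alongside it.
4. Keep categories for plots only, assigned per examination, and say so.

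**Cost.** The model becomes slightly more complex. The change also requires a per-examination summary of the oximetry values to be stored, which should be confirmed. If it is stored, only the analysis wording changes.
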